**Summary**

Between 12-30% of patients with severe malaria die despite rapid killing of malaria parasites with antimalarial drugs. This is because malaria parasites have already caused organ/tissue damage Better treatments are needed to reduce this unacceptably high mortality rate. One strategy to reduce mortality is to use adjunctive treatments (ie given in addition to standard antimalarial drugs) that will reduce/reverse the tissue damage caused by severe malaria. We have previously shown that levels of nitric oxide (NO) and its precursor arginine are low in severe malaria. NO production has been associated with protection from severe malaria in multiple human studies, including the NIHRD-MSHR studies in Indonesia. L-arginine is a naturally-occurring amino acid found in plant and animal protein. It is the only substrate for NO production. Levels of arginine are low in both children and adults with severe malaria, and very low levels have been associated with increased mortality. Because NO has multiple anti-disease properties (reducing cytokine-damage, reducing stickiness of blood vessels, reducing apoptosis), a treatment that will return NO levels back to normal in severe malaria, may improve outcome by reducing/reversing the tissue damage already caused by malaria parasites. We propose that by giving arginine in malaria, the low levels of arginine can be corrected and NO production can be returned to normal, allowing NO to reduce tissue and organ damage. Intravenous L-arginine has been used safely in large doses for over 40 years as a diagnostic test of pituitary function. It has also been used in patients with sepsis, coronary artery disease, peripheral vascular disease, sickle-cell vaso-occlusive crisis with improvement in NO production, vascular function and their clinical condition. These studies also show L-arginine infusion to be cheap and virtually free of adverse reactions, even at doses much higher than we will use in this study. **Our goal**is to determine if L-arginine has potential to reduce tissue damage and improve outcome in severe malaria when added to standard quinine therapy. As the first steps, we plan 3 stages over 3 years:

***Stage 1: Natural history study: time course of recovery of hypoargininemia (and pharmacodynamic measures) in uncomplicated and severe malaria***

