*Arginine: clinical pharmacology:* In healthy humans endogenous arginine is a non-essential amino acid, synthesised from citrulline, which is in turn synthesised from enteral glutamine and glutamate7. However, in acute inflammation such as in sickle cell crisis11,12, severe burns13 and sepsis14, plasma levels of arginine are low and arginine is “conditionally essential” 13,15. Arginine is metabolised by arginases (in hepatocytes and other cell types) to form urea and ornithine, but there is strict segregation of hepatic and plasma arginine pools and only 5% of urea production is derived from plasma arginine7. Arginine is also renally excreted but undergoes almost complete tubular reabsorption16. When exogenous arginine exceeds the renal threshold for tubular reabsorption (eg in supraphysiological dosage), there is additional renal excretion16. The pharmacokinetics of L-arginine are derived from studies of arginine given in large doses only to adults with normal plasma arginine concentrations, where it has been described by non-compartmental analysis16,17. There is apparent evidence for non-linear pharmacokinetics, where a dose-dependent elimination half-life has been reported16,17. The reported half-life for oral and IV arginine ranges from 40-120 minutes (with variability due in part to the non-linearity).16 Reported clearance (CL) ranges from 544-1018 ml/min16. In subjects with normal plasma arginine concentrations, the relationship between pharmacokinetic and pharmacodynamic data (urine NOx and total peripheral resistance) was best described using a linear direct effect model, in which effect was linked directly to L-arginine plasma concentration17.

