Plasma arginine in healthy subjects was not significantly different among different age groups or different ethnic groups25. Our data have shown a mean plasma arginine level for healthy Tanzanian children (n=19) of 122 uM (lower limit of normal 78uM). Mean plasma arginine in American adults (n=23) is 117 uM with lower limit of normal of 59uM25. In Indonesian adults in our previous studies in Jayapura (n=43), mean plasma arginine was 114 uM with lower limit of normal of 54 uM ([name], [name] et al, unpublished data). Hypoargininemia can therefore be defined as levels below 54uM (the lower limit of normal in healthy Jayapura residents). In the Tanzanian data above, there were no differences in fasting or weight-for-age among groups and levels returned to normal by day 3 in adults with severe malaria, despite continuing anorexia. This suggests that our arginine findings are not related to underlying malnutrition or to inadequate dietary arginine ingestion prior to malaria25. The causes of low NO production/monocyte NOS2 and low arginine in severe malaria are likely to be multi-factorial25. In separate studies, we are examining cellular mechanisms of hypoargininemia, including arginase activities and PBMC levels of enzymes involved in synthesis, transport and degradation of arginine. Cytokine responses decreasing NOS2 also diminish factors involved in cellular uptake and biosynthesis of L-arginine.7 Non-plasmodial parasites activate arginases during infection26 but whether *P. falciparum* activates arginases is not yet known. Metabolic turnover may be increased in malaria, similar to that seen in burns13 and sepsis15. ***Irrespective of its cause we hypothesise that hypoargininemia limits NO production in malaria and may contribute to severe disease.***With intracellular NOS activity being critically dependent on adequate circulating L-arginine, and with arginine levels in SM well below the Km for cellular uptake of arginine7 hypoargininemia is likely to result in sub-optimal monocyte, endothelial, and tissue NO production in SM. Moreover, hypoargininemia may enhance8-10 the deleterious oxidative stress described in SM27,28. Strategies to increase NO production (such as L-arginine administration) may improve outcome by ameliorating endothelial dysfunction and decreasing deleterious inflammatory cytokine and oxidative responses. Moreover L-arginine reduces ischaemia-reperfusion injury29, and kills *P. falciparum* *in vitro*30 and *in vivo*31 through an NO-mediated effect. Although hypoargininemia can be defined as levels below 54uM (the lower limit of normal in healthy Jayapura residents), increasing plasma levels within and above the normal range will be expected to increase NO production. However, levels below 600uM (4X Km for CAT transporters) will result in submaximal arginine uptake into cells, and 600uM will therefore be the plasma level for therapeutic target.

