*Interpretation:* Pharmacokinetic models will be fitted to concentration-time and concentration-effect data from studies (a) and (c) using NONMEM (v. 5)51, to provide population parameter estimates, mean parameter values and their between-subject variability where possible. This analysis will include assessment of possible covariate relationships, where parameter values such as clearance may be correlated with patient demographics such as age. A model will be developed that describes the time course of effects of arginine in terms of NO production (plasma NOx/creatinine ratio [systemic NO production] and exhaled NO [pulmonary NO production]), oxidant stress, endothelial function, microvascular flow and gas transfer/physiological deadspace. It is also intended to address biomarkers of effectiveness. **[name] from NIHRD will be invited to the Dept Pharmacy in Brisbane to join the NONMEM modeling for the PK-PD relationships outlined above.**

Safety data from study 2 will be reviewed by an experienced independent data monitoring committee (see appendix) before proceeding to study 3. The pharmacokinetic-pharmacodynamic model developed in study 2 will enable us to predict the dosing and best sampling schedule (both pharmacokinetic and pharmacodynamic) for use in study 3. If the pharmacokinetic-pharmacodynamic model suggests that a higher dose than 12g may be required, a dose of up to 18 g may tested in stage 2 of the study prior to commencing stage 3.

*Potential adverse effects (in study 2 and study 3) and study response:* A number of adverse effects have been previously noted with large *supraphysiological* dosing in subjects with normal plasma arginine levels. These have been infrequent and usually at the standard high dose (≥30g) required to stimulate growth hormone release, **a *dose that will not be used in our studies.*** Arginine is a natural product that has been widely used in subjects with cardiovascular disease, sickle cell disease, and sepsis, with an excellent safety profile. This study primarily examines pharmacokinetic-pharmacodynamic modeling, but will also confirm safety in uncomplicated malaria.

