**Patients with uncomplicated malaria in Indonesia have mean levels of arginine *below* normal, and combined with a dose well below the standard 30g IV dose used in other settings, we do not expect significant adverse effects to occur. Whilst we believe the following adverse effects to be very unlikely, our protocol allows us to detect, and if necessary rectify them:**

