**Possible Adverse Effects and Monitoring and Rescue Treatments Protocols:**

**1. Adverse Effects Documented With Evidence**

*a) Effects on blood pressure:* Most patients receiving arginine have no significant effect on blood pressure. Any effects on blood pressure are usually minimal, even with the 30g IV dose used clinically, much higher than we expect to use in this study16,17. Endothelial NOS expression in severe malaria24 makes it important we monitor this closely. Arginine supplementation in sepsis has not significantly exacerbated hypotension41 despite demonstrated tissue NOS expression in sepsis52. In previous studies, any effect on blood pressure has been minor and seen during the infusion, returning rapidly (within minutes) to normal as soon as the infusion is finished. As outlined in table 2, to monitor for hypotension, the subject’s vital signs including blood pressure will be taken every 10-15 minutes prior to infusion, every 5-10 minutes during the infusion and for 15 minutes after the end of the infusion, then 10-15 minutely for the rest of the first hour after the end of the infusion, and half hourly for the next two hours, then 2-4 hourly thereafter.

Response: If systolic blood pressure falls >25 mmHg or below 80mmHg or if the attending clinician is clinically concerned, the arginine infusion will be stopped and legs elevated. Previous studies using higher doses of arginine than we will use in this study have shown the BP rapidly returns to normal within minutes of stopping the arginine infusion, and this is expected to be all that is required. If SBP persists < 80 mmHg, 0.9% saline will be infused at a rate based on the treating clinician’s clinical judgement.

*b) Electrolyte abnormalities:*

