- *Effect on K+:* Hyperkalemia may result from redistribution of K+ from intracellular fluid to extracellular fluid. In seven of eight normal Italian subjects receiving high dose arginine (30g IV), mean plasma K+ transiently increased by 1.23± 0.17 meq/L (range 0.6-1.7), peaking at 60-90 mins after start of a 30 min IV infusion54. These data excluded one subject who had a “virtually negligible” increase54. Clinically significant hyperkalemia has been reported with large supraphysiological doses in patients with renal failure (30g IV)55 and combined liver failure/renal impairment (again with very high dosing of 59-95g IV)56, in subjects taking spironolactone (an exclusion criterion in this study). Mean plasma K+ in 58 Indonesian subjects with uncomplicated malaria (in our initial NO studies in Jayapura) is at the low end of normal range (3.4 meql/L), with only 1 subject out of 58 having a K+> 4.0 [4.5 meq/L]. Subjects with renal failure or baseline K+≥4.2 meq/L will not be included in studies 2 and 3. Moreover lower doses will be used in both of our studies than the 30g dose used in published studies. Therefore a rise in K+ to ≥ 6.0 meq/L will be very unlikely.

Response: If serum K+ rises to ≥ 6.0 meq/L it will be immediately repeated using the bedside iSTAT to exclude hemolysis of sample. If K+ ≥ 6.0 meq/L or if significant ECG changes of hyperkalemia develop, the infusion will be stopped and subjects will be given 10ml of 10% calcium gluconate for membrane stabilization. This will be followed by continuous ECG monitoring and 10-15 minutely monitoring of K+: if thought necessary by the attending clinician, 10 U of regular insulin will be administered with 25g of IV glucose to induce K+ shift into cells.

- *Hypophosphatemia:*

A clinically insignificant transient fall in serum phosphate is noted with 30g infusions, with the maximum fall below baseline of 1.11 mg/100ml (or 33%), peaking 60 mins after commencement of a 30 min infusion54. In no cases did phosphate levels fall to potentially clinically significant levels (<1 mg/dL)54. We will nevertheless measure phosphate levels at baseline and at 60 mins.

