**Theoretical Adverse Effects With No Documented Events**

*a) Effects on blood glucose:* arginine stimulates both insulin and glucagon release53. Because levels of glucagon increase to levels higher than that of insulin, the net effect in humans is reported to be a slight hyperglycemia32,53. Importantly, despite over 40 years’ of use of intravenous arginine in humans, there are **no** clinical case reports of hypoglycemia ever occurring after arginine infusion.

Hypoglycemia can occur in severe (but not, by definition, in uncomplicated malaria)2, therefore blood glucose will be rigorously monitored in both studies as outlined in table 2: We will use iSTAT cartridges (which use a few microlitres of blood) at the bedside to instantly measure glucose (as well as other electrolytes) prior to infusion, at the end of the 30 min infusion, and 15, 30, 60 and 210 minutes after the end of the infusion. Because levels of glucagon (which increases glucose) are higher after arginine infusion than insulin (which lowers glucose), if anything arginine may help prevent hypoglycemia in malaria. We will be measuring glucose in stage 2 and 3 in uncomplicated malaria, so can report back to the ethics committee the effect on blood glucose in malaria before we give arginine to anyone with severe malaria in future studies. If anything the glucagon effect *increasing* blood sugar is likely be protective.

Response: If blood glucose falls below 4 mmol/L, the arginine infusion will be stopped and 50% dextrose will be administered as per standard RSMM/MoH practice in severe malaria, with blood glucose continuing to be monitored 15 minutely to 60 mins then 30 minutely until 480 mins.

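### The under-30 g arginine dose asserted for both studies is not supported for Study 3: holding 600 µM for 12 hours implies about 40–75 g hydrochloride at the cited clearance

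*Combined protocol and SAP*

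**What the plan says.** The adverse-effects text is headed as applying to Studies 2 and 3. Under Effect on K+, directly after exclusions for those two studies, it states: "Moreover lower doses will be used in both of our studies than the 30g dose used in published studies". The same premise appears elsewhere:

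- The introduction to that text describes 30 g or more as a "dose that will not be used in our studies".
- The expectation of no significant adverse effects, repeated under Ethical issues, is "combined with a dose well below the standard 30g IV dose used in other settings".
- Effect on pH cites an absence of pH change at 30 g and describes that dose as far above what this study will use.
- Two statements are softer. The Summary says "even at doses much higher than we will use in this study", without a figure, and the blood pressure text says "even with the 30g IV dose used clinically, much higher than we expect to use in this study".

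Study 3 (Treatment allocation) gives a 30-minute loading dose and then a 12-hour maintenance infusion. The PK-PD model is to set both doses so as to hold 600 µM. No gram amount or cap is given. The target may be readjusted after Studies 1 and 2, and the data monitoring committee reviews dosing and sampling before Study 3 starts. Under Sample size, the notice promised to the ethics committees covers the number of patients.

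**The concern.** A target concentration held for a fixed time at a given clearance determines an amount of drug. The protocol supplies all three inputs but does not multiply them out, and the product exceeds 30 g.

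This matters most for pH. Arginine hydrochloride carries a stated 4.75 mEq of acid per gram, and the reassurance there compares the study dose with 30 g. If the Study 3 total is above 30 g, the comparison points the wrong way for cumulative acid. The ethics committees would then have approved Study 3 partly on a dose statement that its design does not support, and the one notice they are promised need not correct it.

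**Working it through.** **What reproduces.** The 600 µM target is 4 × 150 µM, the upper end of the cited Km range of 70–150 µM. The acid content is 1,000 / 210.66 = 4.75 mEq per gram of hydrochloride. All stated Study 2 doses (3, 6, 12 g, optionally up to 18 g) are below 30 g. The protocol shows no derivation of an under-30 g dose for Study 3.

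**Inputs.**
- Clearance (Arginine: clinical pharmacology): "Reported clearance (CL) ranges from 544-1018 ml/min".
- Endogenous level in healthy Indonesian adults (Hypoargininemia in severe malaria): "mean plasma arginine was 114 uM", lower limit of normal 54 µM.
- Target 600 µM; maintenance 12 h = 720 min (Study 3).
- Molar mass 210.66 g/mol for the hydrochloride and 174.20 g/mol for the base (standard constants; the first agrees with the protocol's 4.75 mEq/g).

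**Formula.** Maintenance amount = clearance × (target − endogenous level) × 720 min.

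Net of 114 µM:
- Low clearance: 0.544 L/min × 0.486 mmol/L × 720 min = 190.4 mmol = 40.1 g hydrochloride (33.2 g base).
- High clearance: 1.018 × 0.486 × 720 = 356.2 mmol = 75.0 g hydrochloride (62.1 g base).

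| Endogenous level subtracted | Hydrochloride, g | Acid, mEq |
|---|---|---|
| 114 µM | 40.1–75.0 | 190–356 |
| 54 µM | 45.1–84.3 | 214–400 |
| none (gross) | 49.5–92.6 | 235–440 |

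**Comparison with 30 g.** 30 × 4.75 = 142.5 mEq. Net of 114 µM, the acid ratio is 190/142.5 to 356/142.5, about 1.3 to 2.5.

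**Rate.** 40.1/12 to 75.0/12 = 3.3–6.3 g/h, or 16–30 mEq/h. Thirty grams in 30 minutes is 60 g/h, or 285 mEq/h.

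**Loading dose, not counted above.** Volume = clearance × half-life / ln 2. With the cited half-lives of 40–120 min and a rise of 486 µM, the load is about 3.2–18.0 g hydrochloride.

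**Break-even for 30 g of maintenance, net of 114 µM.**
- As hydrochloride: 30 g = 142.4 mmol; 142.4 / (720 × 0.486) gives 407 ml/min, 25% below the lowest cited clearance.
- As base: 30 g = 172.2 mmol; 172.2 / (720 × 0.486) gives 492 ml/min, 10% below it.
- By target, at 544 ml/min: about 478 µM (hydrochloride) or 554 µM (base). At 1,018 ml/min: about 308 µM (hydrochloride).

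**Readings.** Study 3 measures laboratory safety as in Study 2, subject to an optimised schedule. With loading at 0–30 min, maintenance runs from 30 to 750 min. Table 2 names iSTAT readings at 45, 60, 90, 180 and 480 min, then the next morning at 18–24 h. The glucose text adds one at 240 min ("15, 30, 60 and 210 minutes after the end of the infusion", with the infusion ending at 30 min). On those clock times nothing is named between 480 min and 18 h. That leaves 270/720 = 37.5% of maintenance, or 15–28 g and 71–134 mEq, with no named reading.

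**The case against.** The strongest reply is that there is no Study 3 dose to contradict. The model sets it, the target is provisional, and the data monitoring committee reviews it first. The under-30 g statements could be read as commitments that will bind the calculation. This stands in part: the 40–75 g is what the protocol's inputs imply, not a planned dose. But the statements are written as facts that support a safety conclusion, and nothing in Study 3 makes them a constraint.

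The clearance input is also weak. It comes from large doses in adults with normal arginine, with apparent non-linearity, and arginine kinetics in malaria are not yet described. A clearance 10–25% below the cited range would be enough to reach break-even. This stands, and limits the finding to what the cited inputs imply.

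A reader might infer more than the documents support, in three ways:

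- **Raised potassium risk.** The implied total overlaps the 59–95 g that the protocol links to hyperkalaemia, but those patients had liver failure with renal impairment and were taking spironolactone. In the 30 g potassium data the drug ran in over 30 minutes. The comparable element in Study 3 is the loading dose, about 3–18 g. The low baseline potassium, the exclusions and the ECG monitoring still apply.
- **Expected acidosis.** The acid is delivered slowly. The pH argument also rests on unchanged pH in patients with renal failure and on bedside monitoring with a stop at bicarbonate below 15 mmol/L. Entry excludes bicarbonate below 20 or chloride above 106.
- **30 g passed only after the last named reading.** At 544 ml/min, maintenance alone reaches 30 g at about 569 min. A load of 3.2–9.6 g brings this to about 396–511 min, either side of the 480 min reading. At 1,018 ml/min it is about 318 min even without a load.

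Nor is the reading gap a fixed omission. It carries over clock times built for a 30-minute infusion, and Study 3 lets modelling of electrolyte disturbances set its schedule.

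**Conclusion.** The statement is wrong as written, with minor to moderate consequences. Study 2 satisfies it; Study 3, on the protocol's own inputs, does not. The lowest of the cases worked through, free base at the lowest cited clearance net of 114 µM, is 33 g before any loading dose.

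The result assumes that clearance at 600 µM lies within the cited range and that endogenous supply continues unchanged. The salt form of the published 30 g is not stated, so both forms are shown. Leaving out the loading dose is conservative. So is using a healthy baseline, since the protocol says arginine is below normal in these patients.

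The failure is confined to the cumulative-dose comparison, chiefly in the pH argument. No harm is demonstrated, and no estimand, analysis or sample size is affected.

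**What to change.** 1. Limit the under-30 g statements to Study 2 wherever they occur (potassium, pH, the introduction to adverse effects, Ethical issues), and align the softer wording in the Summary and the blood pressure text. Alternatively, set 30 g as an explicit cap on the model-derived Study 3 dose, saying whether it includes the load. A cap may force a lower target, as the break-even figures show.
2. State the expected Study 3 total dose and rate, as hydrochloride, in the dosing submission to the data monitoring committee and in the notice to the ethics committees before Study 3.
3. When the Study 3 schedule is set, include bedside iSTAT potassium, chloride and bicarbonate late in maintenance and at its end (about 750 min). The bicarbonate stop rule can act only on a reading.

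The cost of the wording option is text edits, a dose line in two documents already planned, and one or two extra cartridges per patient with some evening or night staff time. Each cartridge uses only microlitres, so the 25 ml blood limit is not materially affected.
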